**Figure 1 figure1:**
[figure not shown]
Statistical power of detecting a cross-sectional association between heavy occupational lifting and hypertension, as a function of the underlying odds ratio between exposed and unexposed participants in the target population.

**Figure 2 figure2:**
[figure not shown]
Statistical power of detecting an association between heavy occupational lifting at examination n and antihypertensive drug usage or an above median delta of systolic blood pressure (SBP) at examination n+1, as a function of the underlying odds ratio between exposed and unexposed participants in the target population.

The statistical powers of the primary hypotheses are given in Figures 1 and 2. The calculations are based on the above assumptions, the propagation of error formulas, the central limit theorem, and a two-tailed significance level at *P*=.025, for each of the two hypotheses.

### Secondary Analyses

#### Linear Regression on Systolic Blood Pressure

It has been suggested that each mm Hg increase in resting SPB is associated with an approximately 3.5% increased risk of death due to ischemic heart disease (IHD) [13]. It has moreover been suggested that the relative effect of a 1 mm Hg increase is quite independent of the level of SBP; a change in SBP from 120 to 121 would, for example, cause the same relative risk increase as a change from 139 to 140 [13]. From this viewpoint, it would be of interest to estimate the expected effect of heavy occupational lifting on resting SBP in a linear regression model and thereby obtain an estimate that could be directly translated into relative risks of death due to IHD. There are, however, some problems with this approach:

If occupational lifting is associated with risk of hypertension and we exclude participants who are treated for hypertension, then the participants who had been most affected by their occupational lifting status would be more likely to be excluded than the ones who had been least affected, and this would bias the estimation toward unity.

If we do not exclude participants who are treated for hypertension then the potential effects of occupational lifting on BP may be concealed, reversed, or otherwise distorted by effects from antihypertensive drugs and other types of heart medications.

It was the above mentioned problems that made us refrain from linear regression in the primary analyses. We recognize, however, that a conservative estimation of the effect of heavy occupational lifting on resting SBP in a linear regression model may provide meaningful information if the bias is taken into account in the interpretation of the results. We will therefore conduct a secondary analysis, in which the association between heavy occupational lifting and SBP will be investigated, first cross-sectionally and then prospectively (change in SBP [mm Hg] from examination n to examination n+1), by use of linear regression. Observations from participants who are treated with antihypertensive drugs or other types of heart medications will be excluded from an analysis similar to the primary analysis and performed both cross-sectionally and prospectively.

Generalized estimating equations will be used to estimate the parameters. Observations from the same person will be treated as repeated measurements. A first-order autoregressive correlation structure is assumed. Should the estimated covariance matrix fail to converge then we will resort to a variance component correlation structure. The expected difference between the exposed and the nonexposed will be estimated and presented with a 95% CI, based on the empiric SE.

#### Analysis on Other Types of Blood Pressure Measurements

It is presently not known if and how a person’s resting BP is influenced by occupational lifting activities. It is therefore of interest to also regard potential effects of occupational lifting on mean arterial pressure, DBP, and pulse pressure. For this reason, we will repeat the linear regression analyses described above on each of these outcomes. Furthermore, a prospective analysis will be applied where the outcome will be classified as a DBP case, similar to the analysis aforementioned relating occupational lifting to the risk of becoming an SBP case. The DBP case will be defined by the shift from no use of antihypertensive drugs in examination n to use of antihypertensive drugs in examination n+1 or an above median delta value of DBP (DBP in examination n+1−DBP in examination n).

#### Sensitivity to Choice of Comparison Group

According to our primary assessment of exposure, the exposed group would consist of participants whose work entailed heavy occupational lifting combined with walking, some handling of material, or heavy manual work. The comparison group would consist of the rest of the occupationally active participants, regardless of their type of occupational activity. We want to know how sensitive our analyses are to the choice of comparison group after adjustment for the included covariates. To shed some light on this issue, we plan to perform an additional set of linear regressions on SBP. In these particular analyses, we will split the comparison group into three different subgroups and thereby create an exposure variable with 4 instead of 2 categories. The statistical models, covariates, and inclusion criteria will otherwise be the same as they are in our previously defined linear regression analyses. The results will be presented as outlined in Table 6.

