## Introduction

### Background

Hypertension is a major risk factor for cardiovascular diseases [1,2] and is responsible for 14% of all annual deaths globally [1]. The prevalence of hypertension varies across occupational groups, possibly affected by differences in the working environment. One work-related factor that might impose a risk for hypertension is lifting [3,4]. Heavy lifting causes acute large increases in blood pressure (BP) [5]. These increases in BP during heavy lifting are explained by the constriction of the vessels due to contraction of muscle fibers surrounding the vessels as well as the pressor reflex, both leading to an increased peripheral resistance and thereby also an increased BP [5]. Thus, because some workers perform occupational lifting for several hours per day, many days per week, higher BP or hypertension is likely to occur [6]. Yet, scientific knowledge of the relation between heavy occupational lifting and hypertension is limited. Previous studies investigating this relation have found occupational lifting to increase risks for myocardial infarction [3] and ischemic heart disease [4] in population studies including both sexes and workers from white- and blue-collar occupations. However, one study, only including males from blue-collar occupations did not find increased risk for ischemic heart disease from occupational lifting [7]. As the study by Petersen and colleagues [4] found the risks from lifting to be most pronounced among workers with low occupational physical activity (OPA) but high exposure to lifting, it seems that investigations of associations between occupational lifting and risk for hypertension benefit from populations including both sexes and a variety of occupations.

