### Assessment of Exposure

In all 3 examinations, the self-reported information on level of OPA was obtained by asking the question: “Please describe your level of OPA within the past year” with the following response categories: “(1) predominantly sedentary; (2) sitting or standing, some walking; (3) walking, some handling of material; (4) heavy manual work.” If answering 3 or 4, an additional question regarding heavy occupational lifting was applied. The question was: “Do you lift heavy burdens?” with the response categories: “(1) yes and (2) no.” Participants will be classified as exposed to heavy occupational lifting by answering “yes” to the question concerning heavy burdens, and those participants answering 1, 2, and 3 or 4 in combination with not lifting heavy burdens will be classified as the reference group.

Between the examinations of data collection, we do not have any information about their exposure to OPA or lifting. However, for the prospective analysis, a measure of the stability of exposure was accounted for by cross-tabulating the self-reported exposure at examination 3 by exposure at examination 4 and also the self-reported exposure at examination 4 by exposure at examination 5. Among those participants responding to the self-reported exposure to OPA at examinations 3 and 4, 13.4% (329/2459) stated to be exposed to heavy lifting in examination 3 and 12.0% (295/2459) in examination 4. Among those participants responding to the self-reported exposure to OPA at examinations 4 and 5, 8.29% (146/1762) stated to be exposed to heavy lifting in examination 4 and 6.81% (120/1762) in examination 5. An evaluation of the agreement (Cohen kappa) between exposure to heavy occupational lifting in examinations 3 and 4 was .30, and the agreement between exposure to heavy occupational lifting in examinations 4 and 5 was .40, indicating a fair agreement between exposure to heavy occupational lifting across examinations (see Tables 1-4) [12].

**Table 1 table1:** Number of participants who responded to the questions on level of occupational physical activity (OPA) at examinations 3 and 4.

Examination 3 (1991-1994)	Examination 4 (2001-2003)			
	1^a^	2	3	4
1	599	223	45	9
2	173	511	123	8
3	57	210	367	34
4	3	21	26	50

^a^1=predominantly sedentary; 2=sitting or standing, some walking; 3=walking, some handling of material; 4=heavy manual work.

**Table 2 table2:** Number of participants who reported to have heavy occupational lifting at examinations 3 and 4.

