### Primary Statistical Analyses

Logistic regression will be used to estimate the odds of becoming a case from examination n to n+1 as a function of heavy occupational lifting. For the cross-sectional analysis, there will be a possibility of 3 observations per participant, 1 from each examination. For the prospective analysis, there will be a possibility of 2 observations per participant, 1 from the third to the fourth examination and one from the fourth to the fifth examination. The cross-sectional analysis will be controlled for sex, age, BMI, smoking, and education. The prospective analysis will, in addition to the variables of the cross-sectional analysis, be controlled for self-rated cardiorespiratory fitness, vital exhaustion, and BP at baseline. Self-rated cardiorespiratory fitness and vital exhaustion will only be included as covariates in the prospective analysis where the main point of interest is new cases and not prevalent cases as in the cross-sectional analysis. Generalized estimating equations will be used to estimate the parameters. Observations from the same person will be treated as repeated measurements. A first order autoregressive correlation structure is assumed. Should the estimated covariance matrix fail to converge, then we will resort to a variance component correlation structure.

The significance test will be based on the empirical SE and the Wald Statistic. The odds ratio (OR) between the exposed and the nonexposed will be calculated and presented with a 95% CI. The CI will be based on the empiric SE.

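### Sensitivity to the comparison group is checked only in linear SBP models that exclude treated participants, not in the two primary logistic models, where about 86% of reference observations come from workers not asked about lifting

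*Protocol article*

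**What the plan says.** **Exposure.** Under Assessment of Exposure, OPA has four levels. The lifting item was conditional: "If answering 3 or 4, an additional question regarding heavy occupational lifting was applied". Of the rest, "those participants answering 1, 2, and 3 or 4 in combination with not lifting heavy burdens will be classified as the reference group". Levels 1 and 2 therefore count as unexposed without having been asked at that examination.

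**Primary models.** Under Primary Statistical Analyses, both hypotheses use logistic regression fitted by generalized estimating equations (GEE): "The odds ratio (OR) between the exposed and the nonexposed will be calculated and presented with a 95% CI". Both models adjust for sex, age, BMI, smoking and education. The prospective model adds self-rated fitness, vital exhaustion and baseline BP. OPA level is in neither.

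**Outcomes.** Under Assessment of Outcome, current antihypertensive drug use is enough for hypertension, and starting such drugs is enough for an SBP case.

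**The planned check.** Under Sensitivity to Choice of Comparison Group the aim is general: "We want to know how sensitive our analyses are to the choice of comparison group after adjustment for the included covariates". The answer is confined to one type of model: "we plan to perform an additional set of linear regressions on SBP", with the four exposure categories of Table 6. It also takes over the population of the earlier linear analyses: "The statistical models, covariates, and inclusion criteria will otherwise be the same as they are in our previously defined linear regression analyses". For those, under Linear Regression on Systolic Blood Pressure, "Observations from participants who are treated with antihypertensive drugs or other types of heart medications will be excluded".

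**The concern.** The section asks about the analyses in general, but the check it fixes differs from the tested analyses in three ways: outcome scale (mm Hg instead of case status), model (linear instead of logistic) and population (treated participants removed). The third matters most, because participants who are cases through drug use contribute to the primary odds ratios and are absent from the check.

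The primary contrast is mainly lifters against sedentary or sitting/standing workers. Without OPA level in the model, an odds ratio above or below 1 may partly reflect activity level. Under Implications of the Proposed Analysis, a positive association would be read as a physiological effect of lifting that supports prevention. That reading is stronger if the tested odds ratios also hold against workers of similar activity who do not lift.

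A second issue concerns the workers who were not asked. The Background reports from an earlier cohort that risk was most pronounced among "workers with low occupational physical activity (OPA) but high exposure to lifting". Any such workers at OPA 1-2 are counted here as unexposed.

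**Working it through.** **1. The plan's own figures.** These reproduce.
- Exposed share: 1830/11,670 = 15.68%.
- Cases: 0.20 × 11,670 = 2334; 0.55 × 4746 = 2610.
- Prospective numbers after removing 20% hypertensives: 0.80 × 5932 = 4746; 0.80 × 4089 = 3271.
- Variance inflation factor (VIF) = 1 + (observations per participant − 1) × intraperson correlation: 1 + 0.63 × 0.5 ≈ 1.31; 1 + 0.45 × 0.1 ≈ 1.05.

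**2. Make-up of the reference group** (Tables 7 and 8, observations)

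| | Cross-sectional | Prospective |
|---|---|---|
| OPA 1 + OPA 2, not asked | 4407 + 4079 = 8486 | 2113 + 2086 = 4199 |
| Reference = total − lifters | 11,670 − 1830 = 9840 | 5932 − 1039 = 4893 |
| Share not asked | 86.2% | 85.8% |
| OPA 3-4 non-lifters | 2729 + 455 − 1830 = 1354 | 1497 + 234 − 1039 = 692 |

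The text under Differences in the Study Population gives 1638 lifters out of the same 11,670. With that count the cross-sectional share is 8486/10,032 = 84.6%. The two counts need reconciling, but the point holds with either. The prospective OPA counts sum to 5930 rather than 5932, which is immaterial. All shares describe OPA respondents before the BP, drug-use and normotension criteria are applied.

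**3. Where the comparison group is split.** Only in the linear models on SBP and change in SBP. The cut-point and age sensitivity analyses do refit the primary logistic models, but neither splits the comparison group. The later linear analysis that keeps treated participants is still not logistic and is not clearly extended to the four categories.

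**4. Precision of the OPA 3-4 contrast.** Wald test on the log odds ratio, with SE² = VIF × [1/(n₁p₁q₁) + 1/(n₀p₀q₀)]. The detectable OR solves ln OR = (2.241 + 0.842) × SE, for two-sided alpha .025 and 80% power. Assumptions: overall case share 20% or 55% as in the plan, also within the restricted contrast; no covariate adjustment; the 20% baseline exclusion falls equally on all exposure groups.

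| Contrast | Lifters | Comparators | Detectable OR |
|---|---|---|---|
| Cross-sectional, full reference | 1830 | 9840 | 1.24 |
| Cross-sectional, OPA 3-4 non-lifters | 1830 | 1354 | 1.38 |
| Prospective, full reference | 831 | 3914 | 1.28 |
| Prospective, OPA 3-4 non-lifters | 831 | 554 | 1.42 |
| Prospective, OPA 3-4 non-lifters, 1850 participants | 470 | 313 | 1.59 |

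The last row is there because the Results expect fewer than 1850 prospective participants, while Table 5 has 3271. It assumes 1850 × 1.45 = 2682.5 observations, split as in Table 8.

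**5. Misclassified lifters at OPA 1-2, illustration only.** The documents give no lifting share at these levels, so 10-20% is an assumption. With 19% hypertension in the unexposed and a true OR of 1.30, risk in lifters is 23.4%. Hidden lifters make up 0.862 × 10% = 8.6% to 0.862 × 20% = 17.2% of the reference group, whose risk rises to 19.4-19.8%. The observed OR becomes 1.27-1.24.

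**The case against.** **The planned check is not empty.** A reader might infer that Table 6 cannot bear on the primary results at all. The documents do not support that. If the median change is taken over the analysed group, about half of participants are SBP cases through change in SBP alone. The plan assumes 55% cases, so about 50/55, or nine in ten, would arise from the variable that Table 6 analyses. The cross-sectional link is looser, since DBP and drug use also define hypertension. The evidence is real but indirect.

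**Confounding is partly handled.** A reader might also infer that the primary odds ratios simply mix lifting with social position. Education in five categories, smoking, BMI, age and sex are adjusted for, with more covariates prospectively. What remains unadjusted is OPA level, together with any residual confounding.

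**The misclassification shown is modest.** Under the assumed shares it pulls an OR of 1.30 down to 1.27-1.24, which is attenuation and not a spurious positive result. No figure in the documents shows that the reference group would produce a positive finding.

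**The authors saw the issue.** They gave it a section and a dummy table, promised only limited insight, and disclosed the bias from excluding treated participants. This stands, and there is no contradiction to correct. But the same protocol says that problems with linear regression led it away from that model for the primary analyses, and it then relies on that model alone for this question. For cut-points and age it refits the primary models.

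**Conclusion.** The concern holds in limited form, as a worthwhile and cheap improvement and not as an error that invalidates the plan. The check on the comparison group does not touch the odds ratios that are tested, and it drops treated participants, who can be cases in both primary outcomes. About 86% of reference observations among OPA respondents were not asked about lifting (84.6% cross-sectionally with the alternative count of lifters), and OPA level is not adjusted for. The primary odds ratios may therefore partly reflect activity level, and the planned linear models inform on that only indirectly.

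The size of any such effect cannot be derived from the documents. The detectable odds ratios rest on the plan's case rates and variance inflation factors without covariate adjustment, so they indicate feasibility only.

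**What to change.** In addition to the linear models, refit both primary logistic GEE models with the four exposure categories of Table 6, keeping their outcomes, covariates and inclusion criteria. Report the odds ratio of lifters against OPA 3-4 non-lifters, and against each of the other two groups, with 95% CIs. Label this a prespecified exploratory sensitivity analysis that spends no alpha, in line with the plan's handling of secondary analyses.

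State as a limitation that the refit helps to separate lifting from activity level but cannot identify lifters within OPA 1-2: they were not asked, and contrasts with those groups remain open to misclassification.

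The cost is two model fits and one table. No data are lost and the primary tests are unchanged. The OPA 3-4 contrast is less precise, with detectable odds ratios of about 1.38 and 1.42 against 1.24 and 1.28 for the full reference group. If the prospective sample is nearer 1850 participants, the figure is about 1.6 and a null result there would say little. The text should say so beforehand, and the two expected prospective sample sizes and the two counts of lifters should be reconciled.

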#### Sensitivity to the Definition of Hypertension

In our primary cross-sectional analysis, we will define hypertension as the use of antihypertensive drugs or a measured consultation SBP ≥140 mm Hg or DBP ≥90 mm Hg [25]. We recognize, however, that the cut-points could have been defined differently, eg, SBP ≥160 mm Hg or DBP ≥100 mm Hg [25]; SBP ≥180 mm Hg or DBP ≥110 mm Hg [25,26]; and SBP ≥130 mm Hg or DBP ≥80 mm Hg [27].

**Table 6 table6:** Dummy table for the reporting of results of linear regressions on systolic blood pressure (SBP) as a function of occupational physical activity.

Occupational physical activity	Cross-sectional differences in SBP			Prospective differences in delta SBP		
	N^a^	Diff^b^	95% CI	N	Diff	95% CI
Heavy lifting		Ref^c^	—		Ref	—
Walking, some handling of material or heavy manual work but no heavy lifting						
Sitting or standing, some walking						
Predominantly sedentary work						

^a^Number of observations.

^b^Difference in mm Hg.

^c^Reference group.

We want to know whether the OR for hypertension as a function of heavy occupational lifting is sensitive to the definition of hypertension. We will therefore conduct two additional cross-sectional logistic regression analyses, which will be performed in the same way as the primary cross-sectional analysis but with the cut-points SBP ≥160 mm Hg or DBP ≥100 mm Hg and SBP ≥130 mm Hg or DBP ≥80 mm Hg instead of the traditional SBP ≥140 mm Hg or DBP ≥90 mm Hg.

#### Stratification by Age

A potential effect of occupational exposures might be more pronounced among people who are likely to be occupationally active throughout the approximately 10-year period that passes between the baseline and follow-up examinations than it is among people who have fulfilled the requirements for old-age pension (65 years of age) or early retirement (60 years of age) at the time of the follow-up examination. It is therefore possible that this study is more relevant among participants who are younger than 50 years at baseline than it is among those who are 50 years or older. For this reason, we will perform a sensitivity analysis in which the sample is stratified by age at baseline (≥ vs <50 years). The outcome, statistical model, inclusion criteria, and covariates will otherwise be the same as they were in the primary prospective analysis.

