### Criteria for Statistical Significance

The overall significance level will be set at .05. A Bonferroni correction will be applied, due to the similarity of the two proposed hypotheses, which means that each of the two primary hypotheses will be tested at a significance level of *P*=.025. Secondary analyses will be regarded as exploratory and will therefore not be tested for statistical significance, but the precision will be reported by 95% CI. They may influence the interpretation of findings of the primary analyses.

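### The age-stratified analysis asks whether the lifting effect differs by age but yields only two separate odds ratios, with no estimate of their difference

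*Protocol article*

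**What the plan says.** The section Stratification by Age gives a comparative reason for the split: "A potential effect of occupational exposures might be more pronounced among people who are likely to be occupationally active throughout the approximately 10-year period" between the examinations than among those who reach pension or early-retirement age by follow-up. It continues: "It is therefore possible that this study is more relevant among participants who are younger than 50 years at baseline" than among older ones. The analysis follows from that: "we will perform a sensitivity analysis in which the sample is stratified by age at baseline (≥ vs <50 years" as the dividing line. The method is then fixed: "The outcome, statistical model, inclusion criteria, and covariates will otherwise be the same as they were in the primary prospective analysis". The primary model, under Primary Statistical Analyses, is a logistic GEE with lifting as the exposure, and no lifting-by-age term is listed. No ratio of ORs or other comparison between the strata appears elsewhere in the article.

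Criteria for Statistical Significance sets the status of such analyses: "Secondary analyses will be regarded as exploratory and will therefore not be tested for statistical significance, but the precision will be reported by 95% CI". It adds: "They may influence the interpretation of findings of the primary analyses".

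**The concern.** Whether an effect is stronger in one group than in another is answered by the difference between two effects and the uncertainty of that difference. Two stratum ORs, each with its own interval, do not supply it. Each stratum holds roughly half the data, so the two estimates will differ by chance, and one interval may exclude 1 while the other does not even though the effect is the same. With no contrast reported, a reader has only the two intervals to compare by eye. If lifting looked harmful only under 50, that pattern would agree with the stated expectation and could colour the reading of the primary prospective result, although it may be noise.

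**Working it through.** **Inputs.** From Statistical Power and Table 5: 4746 prospective observations on 3271 participants, 55% cases, 15.68% exposed, intraperson correlation .1, variance inflation factor (VIF) 1.05. From Table 8: 5932 observations on 4089 participants before hypertensives are removed; baseline age mean 48.0, SD 11.8. From Differences in the Study Population: 17.52% exposed among prospective responders. From Flow of Participants: fewer than 1850 prospective participants, which disagrees with Table 5, so both sizes are run.

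**Table 5 reproduces.** 5932 × 0.80 = 4745.6; 4089 × 0.80 = 3271.2; 4746 × 0.55 = 2610.3; VIF = 1 + (1.45 − 1) × 0.1 = 1.045, printed as 1.05. The article gives no figure for the age-stratified analysis.

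**Share under 50 (assumed).** The article does not state it. A normal distribution with mean 48.0 and SD 11.8 gives Φ((50 − 48.0)/11.8) = Φ(0.17) ≈ .57. Range tried: .40 to .70.

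**Standard errors.** SE(log OR) = √[VIF / (n × p(1 − p) × e(1 − e))], with p = .55 and e = .1568 in both strata (assumed equal). Here p(1 − p) × e(1 − e) = .2475 × .1322 = .0327.
- Under 50: n = .57 × 4746 = 2705; SE = .109
- 50 or over: n = 2041; SE = .125
- Difference in log ORs: √(.109² + .125²) = .166

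**Chance range of the ratio of ORs when the true OR is common.** exp(±1.96 × .166) = 0.72 to 1.38. A true ratio of about exp(2.80 × .166) = 1.59 would be needed for 80% power at two-sided 5%.

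**How often exactly one stratum interval excludes 1.** For a common OR θ, each stratum has P = Φ(ln θ/SE − 1.96), plus a negligible lower tail, and P(exactly one) = P₁(1 − P₂) + P₂(1 − P₁), treating the strata as independent. At θ = 1.25: P₁ = .53, P₂ = .43, exactly one = .50; only the younger stratum = .30.

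| Scenario | SE of contrast | Chance range of ratio | Exactly one, θ = 1.2 / 1.25 / 1.3 / 1.4 |
|---|---|---|---|
| 4746 obs, 15.68% exposed, 57% under 50 | .166 | 0.72–1.38 | .46 / .50 / .48 / .30 |
| same, 40% under 50 | .168 | 0.72–1.39 | .46 / .51 / .49 / .32 |
| same, 70% under 50 | .179 | 0.70–1.42 | .48 / .54 / .54 / .41 |
| 4746 obs, 17.52% exposed, 57% under 50 | .159 | 0.73–1.36 | .47 / .51 / .46 / .26 |
| 1850 × 1.45 ≈ 2680 obs, 15.68% exposed, 57% under 50 | .221 | 0.65–1.54 | .34 / .42 / .48 / .49 |

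Outside that band of ORs, discordance is much rarer at 4746 observations: about .10 at θ = 1.0 and .13 at θ = 1.5.

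**Illustration (hypothetical ORs, base-case SEs).** OR 1.30 (1.05–1.61) under 50 and OR 1.10 (0.86–1.41) at 50 or over look different. Their ratio is 1.30/1.10 = 1.18, with 95% CI 0.85–1.64.

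**The case against.** The best defence is that this is one exploratory sensitivity analysis in a condensed article, that a separate analysis plan could add a contrast, and that a reader can nearly work out the ratio from the two printed ORs. In part this stands. The analysis carries no alpha and touches no primary test. But the section does more than leave a detail open: it gives a comparative reason and then fixes the model as otherwise that of the primary analysis, which has no term to answer it. A hand-calculated ratio also ignores people who contribute one observation under 50 and a second at 50 or over, which the plan's two observations per person about 10 years apart allow.

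Some stronger readings are tempting and not supported:
- *That the analysis is meant to show a stronger effect under 50.* The wording is conditional throughout, so it is meant to examine whether this is so. It can also fairly be read as wanting an estimate in the group most likely to stay exposed, which a stratum OR does supply.
- *That the plan will judge the strata by whether each interval excludes 1.* It says no such thing. Secondary intervals are given for precision and not as tests. The point is only that nothing better is provided for the comparison.
- *That misleading discordance is likely whatever the truth.* It is common only for modest shared ORs.
- *That the permission for secondary results to influence interpretation licenses a claim about age.* It is a general sentence about all secondary analyses.

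It is also right that a single product term imposes common covariate effects across ages, so its ratio need not equal the ratio of separately fitted stratum ORs. The fix allows for this.

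**Conclusion.** The point holds as a minor one. The plan poses a between-group question and specifies a method that does not estimate the between-group difference. On the plan's inputs that difference is imprecise: a ratio of ORs anywhere from about 0.72 to 1.38 is compatible with no difference by age, and wider still (about 0.65 to 1.54) with the smaller sample size given under Flow of Participants. For a common OR of 1.2 to 1.4, exactly one stratum interval excludes 1 in about 30% to 50% of cases in the base case, and about 25% to 55% across the assumed age shares and both exposure figures at 4746 observations.

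These sizes rest on the assumed share under 50, equal exposure and case proportions in both strata, independent strata, and no allowance for covariate adjustment, which would probably widen the standard errors somewhat. The two primary hypotheses and their .025 levels are not affected.

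**What to change.** In Stratification by Age, add that one prospective GEE model will be fitted to both age strata together with a lifting-by-age-group term. Include age-group-by-covariate terms as well if the ratio is meant to agree closely with the stratum-specific ORs. The joint model also accounts for people who contribute an observation to each stratum. Report the ratio of ORs with its 95% CI, without a test, beside the two stratum ORs, and state that any claim that the effect differs by age rests on that ratio. This respects the existing rule for secondary analyses.

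The cost is one extra term (more if covariates are allowed to differ by age), with no new data and no alpha. The downside is that the contrast will be imprecise. The report should say so, and should not read a wide interval as evidence that the effect is the same at all ages.
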